## Abstract

**Background:**

Distal radius fractures (DRF) account for nearly one-fifth of all fractures in older adults, and women experience them 5× as often as men. Most DRF occur with low impact injuries to the wrist with an outstretched hand, and are often managed via closed treatment and cast immobilization. Women sustaining a DRF are at risk for upper limb immobility, sensorimotor changes, edema and type I complex regional pain syndrome (CRPS). Since CRPS onset is likely influenced by alterations in the brain’s somatosensory region, a rehabilitation intervention, Graded Motor Imagery (GMI), aims to restore cortical representation, including sensory and motor function, of the affected limb. To date, there are no studies on the use of GMI in reducing risk of or preventing the onset of type I CRPS in women with DRF treated with cast immobilization. Due to a higher likelihood of women with this injury developing type I CRPS, it is important to early intervention is needed.

**Methods/design:**

This article describes a six-week randomized comparative effectiveness trial, where the outcomes of a modified GMI program (mGMI) + standard of care (SOC) group (*n* = 33) are compared to a SOC only control group (*n* = 33). Immediately following cast immobilization, both groups participate in four 1-h clinic-based sessions, and a home program for 10 min three times daily until cast removal. Blinded assessments occur within 1 week of cast immobilization (baseline), at three weeks post cast immbolization, cast removal, and at three months post cast removal. The primary outcomes are patient reported wrist/hand function and symptomology on the Patient Rated Wristand Hand Evaluation, McGill Pain Questionnaire, and Budapest CRPS Criteria. The secondary outcomes are grip strength, active range of motion as per goniometry, circumferential edema measurements, and joint position sense.

**Discussion:**

This study will investigate the early effects of mGMI + SOC hand therapy compared to SOC alone. We intend to investigate whether an intervention, specifically mGMI, used to treat preexisiting pain and motor dysfunction might also be used to mitigate these problems prior to their onset. If positive effects are observed, mGMI + SOC may be considered for incorporation into early rehabilitation program.

**Trial registration:**

This trial is registered at ClinicalTrials.gov with identifier NCT02957240 (Approval date: April 20, 2017).

## Background

### Epidemiology, etiology, and medical treatment of DRF

Distal radius fractures (DRF) are the most common fractures of the upper extremity in the United States [1–3]. These fractures account for up to 18% of all fractures in persons over the age of 65 years and are nearly 5 times more likely to occur in women than in men [4]. With advancing age, the incidence for women increases rapidly after age 55, almost doubling every 10 years until 90 years of age [5] with the average age of occurrence being 56 years [6]. Women in an urban setting are 30% more likely to sustain a DRF than those in a rural setting [7]. The risk of sustaining a DRF is 20% greater in winter months (*RR* = 1.2), and 45% more likely to occur on days that begin with snow and ice on the ground (incidence rate ratio, 1.45) [8–10]. Given the globe’s aging population, osteoporotic fractures of the wrist, humerus, spine or hip are expected to increase further in the coming years, and the aftercare will be an increasing burden on healthcare resources [11]. Typical medical care for non-operative DRF involves closed reduction in the emergency department or orthopedic office, followed by immobilization in a forearm based cast for four to six weeks, and early active range of motion to non-immobilized joints [12, 13].

### Function and impairment following DRF

Women sustaining a wrist fracture are likely to have a clinically important functional decline in self care, productivity, and leisure performance [14]. Disability levels based on the Patient Rated Wrist and Hand Evaluation (PRWHE) are reported to be high (75%) at the first week after DRF, and modertate (43%) at 8 weeks post injury [15]. Wrist and forearm active range of motion (AROM) and hand grip strength are the most commonly assessed physical impairments in all persons who are status-post DRF and are, on average, reduced by 40 to 50% at eight weeks post injury [16]. A case-control designed study revealed that distal radius fractures in both men and women have large effects (ƞ^*2*^ = .49) on grip strength relative to matched controls [17] and, in turn, grip strength is a significant predictor of wrist function as measured by the PRWHE [18, 19]. Recent research also suggests that persons with DRF experience significant impairments in sensorimotor functions such as wrist joint proprioception and moving light touch awareness [17]. There are also indications that sensorimotor functions have significant associations (fine motor: *r* = −.52, joint position sense error: *r* = .63) with pain levels [17].

### Type I complex regional pain syndrome and DRF

Resting pain and pain with activity are common aftereffect following DRF and have been documented to persist in 32.6 and 41.9% of cases respectively at two years post injury [20]. At the time of initial follow up after first definitive medical/surgical treatment of DRF, 81% of persons have been reported to describe having “severe” to “very severe” pain [15].

Type I complex regional pain syndrome (CRPS) is a condition that presents following an injury or illness where nerves are not damaged and is characterized by regional pain, increased sensitivity to touch, swelling, and impairment of motor function that are out out of proportion relative to the extent and location of the original injury/illness [21–24], and has been reported to occur in as many as 37% of persons who sustain DRF [25]. Jellad et al. [25] report that women are 5.8 times more likely than men to develop CRPS after DRF. Persons who sustain low to medium energy impact DRF are 7.7× more likely to develop CRPS than those who sustain high impact fractures, [25]. Additionally, Moseley et al. [26] report that persons with a 0–10 numerical pain scale (NPS) rating of greater than 4 within one week after closed reduction and casting for DRF were 15.1 times more likely to develop CRPS, than those with less than a 5/10 NPS rating.

Many theories exist on the mechanisms for developing Type I CRPS [27]. Recent evidence indicates that CRPS likely has a component mediated by the cerebral cortex [28, 29]. Neuroimaging studies have revealed CRPS-associated shrinkage of the areas of the primary somatosensory cortex (S1 and S2) that represent the painful limb [30, 31]. These cortical changes may be linked with pain sensitization [28, 30]. Other researchers have illustrated disinhibition of the motor cortex and a disrupted body schema in persons with CRPS [32, 33]. Peripheral sensorimotor changes such as those observed by Karagiannopoulos et al. [17] may be indicative of cortical changes occurring following DRF and cast immobilization.

As many as 37–58% of persons undergoing closed treatment and cast immobilization following DRF go on to develop Type I CRPS [34, 35]. These numbers justify attention, given that most DRF are managed non-surgically via closed reduction and cast immobilization [36, 37]. Therefore, it is important to tailor therapeutic interventions for DRF that address or prevent development of CRPS. Recent evidence suggests that CRPS may develop due to central nervous system changes [27]. Thus, modulation cortical activity might be a noteworthy therapeutic avenue for individuals at risk of developing a CRPS.

### Movement representation techniques

Interventions designed to address centrally mediated pain and motor dysfunction are referred to as *Movement Representation Techniques (MRT)* [38]. These therapies involve observing or imagining normal and pain free movements, which may be performed simultaneously with sensory stimulation and active motion. The aim of MRT is to facilitate pain free movements of a painful limb [38]. MRT include mirror therapy (MT) and graded motor imagery (GMI). GMI is a multidimensional MRT and consists of three intervention phases: 1) limb laterality recognition, 2) Explicit motor imagery, and 3) the aforementioned, MT. Phase 1 involves viewing images of upper limbs and identifying if they are right or left limbs. In the absence of worsening limb symptomology and after proficiency in identifying limb segments has been established, participants transition into phase 2. Phase 2 involves viewing of images of upper limbs and imagining that the affected limb segment is assuming the postures depicted absent pain. Providing that symptoms are controlled, after 2 weeks participants transition into phase 3. In phase 3 (MT), the mirror image of the unaffected limb is observed engaging in various postures. This phase is completed in 2 weeks. All phases progress participants through imagining, and viewing movements that are least to most likely to proke painful experiences.

#### MRT in CRPS

Current evidence provides support for MRT for pain reduction when used in rehabilitation. A meta-analysis found that MRT were effective in reducing pain (*SMD* = 0.82 and disability (*SMD* = 0.72) in persons with chronic pain syndromes [38]. The authors recommended that MRT, particularly MTand GMI, should be considered for patients with CRPS. The aforementioned MRT, MT, has been successful for persons with acute Type I CRPS [39]. It is suggested that patients activate cortical networks by imagining pain free movement and sensation of the affected limb prior to introducing MT [40, 41]. Persons with chronic type I CRPS who performed GMI experienced decreased pain and swelling [F (1,11) = 57] as early as two weeks following implementation and had sustained positive effects on pain (F(3,46) = 8.701) and function (F(3,46) = 7.327) at 6 months follow-up [40].

#### MRT and DRF

Preliminary evidence supports MRT to address pain and physical function in persons with distal radius fracture. Frenkel et al. [42] evaluated the effect of “explicit mental imagery” on wrist and forearm active range of motion when provided to healthy adults during a period of casted wrist immobilization. Compared to a no-treatment control group, those in the imagery group had significantly better wrist extension [*F* (1,16) = 33.375] and ulnar deviation [*F*(1,16) = 7.776] than controls [41]. A study of patients with finger injuries who performed MRT in addition to traditional occupational therapy (OT) interventions indicated improved ROM as measured by a goniometer (*t* = 7.8) and a reduction in disability as measured by the Disabilities of the Arm, Shoulder and Hand (DASH) questionnaire (*t* = − 4.79) [43, 44].

Bayon-Calatayud et al. [45] carried out a randomized controlled trial in 22 patients with closed DRF managed surgically or conservatively. Two groups completed a conventional OT regime while one (experimental) group also completed MT. The outcomes measured were pain, active wrist extension, and disability. No statistically significant differences were found between groups on these measures. However, the findings were limited by 1) a heterogeneous sample of surgical and non-surgical patients without any mention of the baseline characteristics of either group, 2) participants not being blinded to group assignment, 3) a non-descript treatment protocol, 4) no reporting of the temporality of the initiation of the study relative to the injury, and 5) the use of a unidimensional MRT (i.e., MT only). At present, there is paucity in the literature on the use of MRT to prospectively address pain, sensorimotor dysfunction, and disability in persons with DRF and what exists is limited in by its methodology and intervention unidimentionality.

### Rationale for the present study

The upper limb rehabilitation literature is rich in restorative approaches (i.e., resolving impairments when already present). However, little is known about strategies to prevent upper limb, impairment, disability and pain. Recent longitudinal studies indicate that as many as 1/3 to nearly 1/2 of all persons who undergo closed treatment of DRF develop type 1 CRPS [24, 25] and 80% of these patients are women [25]. Current evidence indicates that cortical changes in upper-limb sensory andsensorimotor representation occur within days or weeks during immobilization [46–48], and these changes appear to mimic cortical changes in persons with type I CRPS. A multidimentional MRT, Graded motor imagery (i.e., laterality training, motor imagery and mirror therapy), has emerging support in the literature as a restorative treatment strategy for patients with CRPS [38, 39, 41, 42, 44], however, studies have not examined GMI as a treatment strategy to prevent the onset of CRPS. Implementation of the present protocol will allow investigation into the effects of a modified GMI (mGMI) intervention during the cast immobilization period for women with closed DRF.

## Methods

### Objectives and hypotheses

#### Primary objective

To determine if women at risk for CRPS development after closed treatment of DRF who participate in a mGMI and SOC hand therapy have differing function, pain, upper limb impairments, and counts of CRPS diagnoses following cast removal, and at 1 and 3 months when compared to those who receive only the SOC.

#### Hypothesis

We hypothesize that the combined GMI/SOC intervention will have a positive effect on disability, pain and upper limb impairments at 1 month following cast removal, and counts of CRPS diagnoses at 3 months post cast removal when compared to SOC alone.

### Design

This is a protocol for a randomized comparative effectiveness trial, where the therapy outcomes of two six-week long intervention programs, aSOC only programand an mGMI+SOC program, are compared. The experimental design will be as is described in Table 1.

**Table 1 Tab1:** Experimental design

	Baseline	Weeks 1–3	Week 3	Week 4–6	Cast Removal	4 weeks after cast removal	12 weeks after cast removal
R	O_1_	X	O_2_	X	O_3_	O_4_	O_5_
R	O_1_	X	O_2_	X	O_3_	O_4_	O_5_

Key: X = treatment; O_1_ = pretest; O_2_, O_3_, O_4_, O_5_ = posttests; R = randomization

### Participants

To ensure that criteria for participation are met, patients will be recruited from outpatient clinics staffed by physicians specializing in Orthopaedic, Sports and Family Medicine. The clinics are associated with a large public university in the Midwestern United States. At the time of the first orthopaedic treatment for closed DRF, patients will be offered the opportunity to participate. Prior to enrollment and allocation, oral and written informed consent will be sought. We will seek to enroll 66 participants who have received closed treatment of a distal radius fracture. Through use of a block randomization method, participants will be allocated to a SOC intervention (*n* = 33) group or a SOC + mGMI (*n* = 33) group. Following the consent process, the PI, not a blinded evaluator or interventionist, will actuate the randomization through use of a random block assignment generator [49]. To ensure partcipants are and remain blinded to allotment, participants will be informed that they will be randomized to one of two “occupational therapy treatment approaches” and will be asked not to discuss their treatments with others enrolled in the trial. Evaluators will be blinded to allocation. The feasibility of enrolling these numbers is high given that from 2013 to 2015, the aforementioned Orthopaedics clinic alone cared for an average of 218 women a year who met the below described inclusion criteria. These numbers are likely attributable to the characteristics of the area served by this health system (i.e., urban, northern latitude with slippery weather conditions) which are associated with increased incidence of DRF [7, 9, 10]. The proposed flow of participants from enrollment to completion is reflected in Fig. 1.

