##### Protocol fidelity

The PI will oversee regularly scheduled checks of both our outcome assessors and our interventionists. At each check, the PI will use a protocol checklist to document the number of evaluation and intervention protocol deviations and provide real-time feedback.

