In a manner consistent with that described of Walenkamp et al. [73], an achor-based approach to determining the MCID of the PRWHE and SF-MPQ will be taken through use of the Patient’s Global Impression of Change (PGIC) [74] scale as the anchor. The PGIC is a seven-point Likert scale, ranging from ‘very much improved’ to ‘very much worse’, and will be administered at the time of cast removal. The Minimal detectable change (MDC) of these two measures will be determined through use of the statistical methods described by Walencamp et al. [73].

All statistical analyses will be conductedby a PhD biostatistician who will employ the use of the Statistical Analysis System software (SAS, version 9.3, 2011; SAS Institute, Cary, NC). All analyses will be performed on an intent-to-treat basis. Two-sided tests with *p*-value less than 0.05 will be considered statistically significant.

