### Adverse events

At each contact with the participant, the will seek information on adverse events by specific questioning and, as appropriate, by examination. Information on all adverse events will be recorded immediately in the source document, and also in the appropriate adverse event module of the case report form (CRF). All clearly related signs, symptoms, and abnormal diagnostic procedures results will be recorded in the source document. Reports of all serious adverse events (including follow-up information) will be submitted to the IRB within 10 working days if it falls under the UPIRTSO guidelines. Copies of each report and documentation of IRB notification and receipt will be kept in the Clinical Investigator’s binder. A second copy will be sent to the sponsor.

The PI will be responsible for 1) collecting, reporting, and risk management of adverse events, 2) data collection, entry, transmission and analysis, 3) site coordination and enrollment, 4) regulatory issues such as IRB actions, and conflict of interest disclosures, and 5) reporting the interim analysis to IRB. All collaborators will be immediately notified of any adverse events occur.

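### One unblinded PI randomizes in blocks, is responsible for enrollment and gives feedback to the blinded assessors, so the stated roles do not secure concealment and put assessor blinding at risk

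*Protocol article*

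**What the plan says.** All references are to the protocol article.

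- **Randomization (Participants).** Allocation is by blocks, 33 per group. After consent, the PI, who is stated to be neither a blinded evaluator nor an interventionist, "will actuate the randomization through use of a random block assignment generator". Evaluators are to be blinded, and participants are told only that they will receive one of two therapy approaches.
- **Approach to patients (Participants).** "At the time of the first orthopaedic treatment for closed DRF, patients will be offered the opportunity to participate". The person who makes the offer is not named. Consent comes before enrollment and allocation.
- **Order of events (Design, Table 1).** In both rows the randomization symbol stands before the pretest.
- **PI duties (Adverse events).** The PI's listed responsibilities include "site coordination and enrollment" and "data collection, entry, transmission and analysis".
- **Training (Intervention procedures).** The PI trains the evaluator and the interventionists and tests their competency before the trial starts.
- **Checks during the trial (Protocol fidelity).** The PI oversees regular checks of assessors and interventionists alike, and at each check will "document the number of evaluation and intervention protocol deviations and provide real-time feedback".
- **Check of the blind (Blinding).** Participants and the evaluator give their opinion of the allocation at cast removal.

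**The concern.** The Participants section deliberately keeps the randomization away from evaluators and interventionists. Other sections then connect the person who randomizes to enrollment, to treatment delivery, to the assessors and to the data. No separation between these roles is stated.

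Two things are at stake.

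**Entry.** Eligibility includes a pain rating above 3/10 within a week of first management, and the Inclusion criteria section links this factor to CRPS risk. If someone with influence over entry can anticipate the next assignment, prognosis can differ between arms from the start. Analysis cannot reliably repair that.

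**Assessment.** The evaluator administers the questionnaires and measures motion, grip, finger edema and joint position sense. The CRPS diagnosis is a clinical judgement. Feedback in real time from someone who knows the allocation is a route by which it could reach an assessor. The SF-MPQ is also measured at baseline. If baseline follows randomization, that value is collected when allocation already exists and is known to some staff, and it then enters a model of change over time.

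**Working it through.** The plan gives no figure on this point, so there is none to reproduce. The check has two parts.

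**1. Roles set side by side**

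| Function | Who, and where stated | Would knowledge of allocation matter? |
|---|---|---|
| Responsible for enrollment | PI (Adverse events) | Yes, if upcoming assignments can be anticipated |
| Runs the block generator | PI (Participants) | This person knows each assignment once it is made |
| Checks interventionists | PI oversees (Protocol fidelity) | Watching delivery of mGMI + SOC or SOC can reveal the arm |
| Checks assessors, with feedback | PI oversees (Protocol fidelity) | Yes: the assessors are to stay blinded |
| Responsible for data collection | PI (Adverse events) | Yes, for the same reason |

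The sequence is consent, then randomization (Participants), then pretest (Table 1). Of the three primary outcomes, Table 2 has only the SF-MPQ at baseline.

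The blinding questionnaire is given at cast removal. The hypotheses concern 1 and 3 months after removal, so the questionnaire cannot detect unblinding that happens between removal and those visits.

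**2. How predictable blocks could be**

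Inputs: 1:1 allocation and 66 participants (Participants). Block size is not stated, so 2, 4 and 6 are assumed. It is further assumed that block size is fixed and known, and that past assignments are known.

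Take a block of 2m with m per arm. An assignment is certain when every place left in the block belongs to the same arm, that is, when it lies in the block's final run. The expected number of assignments to one arm after the last of the other is m/(m+1). Adding both arms, the expected final run is 2m/(m+1), so the share certain is

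[2m/(m+1)] / 2m = 1/(m+1).

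- Block 2 (m = 1): 1/2 = 50%
- Block 4 (m = 2): 1/3 = 33%
- Block 6 (m = 3): 1/4 = 25%

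Check for block 4 by listing: AABB and BBAA have 2 certain places each; ABAB, BABA, ABBA and BAAB have 1 each. The total is 8 of 6 × 4 = 24 places, or 33%.

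The hit rate of always guessing the arm with more places left, counting ties as one half, is 75%, 71% and 68% for blocks of 2, 4 and 6, against 50% under full concealment. For block 4, the four places give 1/2, 2/3, 2/3 and 1, with mean 2.833/4 = 0.708.

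**The case against.** The strongest reply is that the article describes the procedure thinly and does not describe a faulty one.

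- **Enrollment.** A reader might infer that the PI personally decides who enters. The text does not say so. The Adverse events section lists accountabilities, and patients are approached in clinics by someone unnamed. This stands.
- **Concealment.** A reader might infer that allocation is not concealed, or that the PI knows 100% of upcoming assignments. Neither is supported. Consent precedes allocation, and nothing says that the PI holds a list or sees ahead. Block size and the holding of the sequence are details that an article may leave to the full protocol, so their absence is not the point here. This stands too.
- **Assessor blinding.** A reader might infer that assessors are unblinded. No disclosure is described, evaluators are stated to be blinded, and a questionnaire tests the blind. The Budapest assessment is made by an orthopaedist, while Outcome measurements gives all measures to a single blinded OT, so it is unclear whether the PI's feedback reaches that rater. Blinding is therefore exposed to risk but not shown to be broken.
- **Baseline.** The baseline assessor is blinded and participants are described as blinded, which limits the harm of randomizing first. It does not remove a reason to reverse the order.
- **Analysis.** A reader might see a contradiction between the PI's responsibility for analysis and the line "All statistical analyses will be conductedby a PhD biostatistician". A PI can be accountable for work that a biostatistician carries out, and this has no bearing on concealment.

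None of this removes the combination of roles. It is what the article states, and does not depend on detail left out.

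**Conclusion.** The point holds in limited form. As written, one person who knows the allocation runs the block randomization, is responsible for enrollment and data collection, and oversees checks of both interventionists and assessors with real-time feedback. Those roles do not secure concealment and put assessor blinding at risk.

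The document does not show that concealment or blinding has failed, and no size of bias can be derived from it. The 50%, 33% and 25% figures are scenarios: they need a fixed, known block size of 2, 4 or 6 and knowledge of past assignments. If blocks vary or their size is unknown, and each assignment is released only after irrevocable enrollment, the risk is much lower. A safer arrangement is available with staff and software that the article already names, so the change is worth making.

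**What to change.** 1. The trial biostatistician generates the list with randomly varying block sizes that are not disclosed to site staff, and loads it into REDCap, which the Data management plan already specifies.
2. REDCap releases each assignment to the interventionist only, and only after consent, eligibility (including the pain rating) and the baseline assessment are recorded. Table 1 and the Participants section are reworded so that baseline precedes randomization.
3. The fidelity duties are split among existing staff so that whoever gives feedback to the assessors does not know allocation. Moving the list to REDCap is not enough for this, because the PI also oversees checks of the interventionists and may learn the allocation that way.

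The cost is a few hours of REDCap set-up, some reassignment of duties and revised wording. No visits are added and the sample size does not change.

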### Intervention procedures

DRF will be managed as per the American Academy of Orthopedic Surgeons guidelines [13]. Upon enrollment in the study, participants will be randomized to an mGMI +SOC group or a SOC only group. The SOC group includes a combination of clinic and home based programming to address hand, elbow and shoulder motion as well as edema control whereas the mGMI +SOC group receives the same SOC programming in addition to MRT interventions intended to maintain the affected limb’s cortical representation. Participants in both groups will complete four clinic-based intervention sessions of an hour each across a 6 week period where thefocus will be on facilitating home program competency and advancement as indicated. The first session will occur within one week of cast treatment and home programming will supplement these clinical sessions. The entire therapy protocol for each group is standardized and manualized to ensure intervention fidelity. SOC and all phases of mGMI home programming are standardized and are to be provided in the form of written materials. The format will be one on one with the interventionist and will involve instruction in home programming as described below. All interventions will be carried out by certified OTs, including a certified hand therapist. Table 1 illustrates the intervention timeline. To enhance intervention fidelity both interventions are protocolized and manualized and the evaluator all interventionists will undergo formal training by the PI. Prior to the initiation of the trial, the PI will conduct a competency assessement of the evaluator and the interventionists.

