##### Phase 1 (left/right discrimination)

When presented with a stack of 50 photos of hands, wrists, and forearms in various postures and orientations (Fig. 2), the participant, without adjusting the cards’ positioning, will determine spontaneously whether it is a right or left upper limb and sort the cards into 2 separate piles. During the clinic session of week two, or when the participant is ready, they will be progressed to the next phase.

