##### Blinding

To evaluate the effectiveness of the blind, participants and the evaluator will complete a questionnaire related to their opinion of the allocation at the time of cast removal.

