### Limitations and future study

This protocol is not without some limitations. Participants will not be screened for motor imagery abilities. This was a decision made to avoid use of time-consuming research tools, avoid further restricting elgibility, and because persons with cognitive and right-left discrimination impairments (i.e., Dyslexia) who are subsequently predisposed to challenges with GMI will be screened out. For ethical reasons, the control group in the proposed study will receive standard care and thus, this study does not invole a no-treatment or sham comparison group.

Future study would include additional randomized control trials to investigate 1) the most effective treatment intensity and duration for the protocol, and 2) the combined effectiveness of this and other rehabilitative interventions.

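### Participants cannot be blinded to allotment when only one arm gets cards, imagery and a mirror box and there is no sham; at most they do not know which programme is under test

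*Protocol article*

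**What the plan says.** All references are to the protocol article.

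- **Participants** sets out measures "To ensure partcipants are and remain blinded to allotment". There are two: "participants will be informed that they will be randomized to one of two" occupational therapy approaches, described neutrally, and they "will be asked not to discuss their treatments with others enrolled in the trial". The same section says evaluators are blinded.
- **Intervention procedures** states that the "mGMI +SOC group receives the same SOC programming in addition to MRT interventions".
- **Phase 1 (left/right discrimination)** opens the mGMI home programme: "When presented with a stack of 50 photos of hands, wrists, and forearms", the woman sorts them into left and right. Phase 2 is imagined movement from the cards. Phase 3 uses a mirror box.
- **Limitations and future study** says that "this study does not invole a no-treatment or sham comparison group" and gives an ethical reason. It does not mention what this means for participant blinding.
- **Blinding** provides the check: "participants and the evaluator will complete a questionnaire related to their opinion of the allocation at the time of cast removal". Table 2 shows it at that visit only.
- **Hypothesis** expects the benefit on function, pain and impairment "at 1 month following cast removal, and counts of CRPS diagnoses at 3 months post cast removal".

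**The concern.** Blinding to allotment means that a participant does not know which of the two treatments she is having. A neutral name for both arms cannot achieve that when the treatments look and feel different to the person doing them. It can only conceal which of the two the investigators hope will do better.

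The difference matters because blinding the assessor does not protect an outcome that the participant reports herself. A reader who accepts the stated blinding would give the self-reported results more weight than the design supports. The protocol treats the issue as serious elsewhere: in the section MRT and DRF it lists unblinded participants among the weaknesses of an earlier randomised mirror-therapy trial in 22 patients. As worded, it suggests that the present trial has removed that weakness.

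**Working it through.** This is a design point, and the claim rests on no figure in the plan. The check sets the sections side by side.

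**1. Can a participant tell the arms apart?**

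| Component | SOC | mGMI + SOC | Section |
|---|---|---|---|
| Four one-hour clinic sessions | yes | yes | Intervention procedures |
| Home exercise and elevation | yes | yes | Home program |
| Photo cards, imagery, mirror box | no | yes | Modified GMI home program, Phases 1 to 3 |
| Imitation of these | none | not applicable | Limitations and future study |

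The extra home practice is 10 minutes, three times a day, six days a week: 10 × 3 × 6 = 180 minutes a week in one arm only. Neither masking measure hides this from the woman doing it. What they can hide is that this part is the experimental one.

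**2. Which primary outcomes can expectation reach?**

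- PRWHE: a patient questionnaire, wholly self-reported.
- SF-MPQ: a patient questionnaire, wholly self-reported.
- Budapest criteria (Table 3): criterion 1 is continuing pain and criterion 2 is reported symptoms, but criterion 3 requires signs displayed at the evaluation. Reported symptoms alone cannot produce a diagnosis.

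So two of the three are fully exposed and one in part.

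**3. Which visits does the check cover?**

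| Primary outcome | Cast removal (questionnaire given) | 4 weeks after | 12 weeks after |
|---|---|---|---|
| SF-MPQ | collected | collected | collected |
| PRWHE | collected | collected | collected |
| Budapest criteria | collected | collected | collected |
| Blinding questionnaire | yes | no | no |

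Cast removal is itself a primary-outcome visit, and the Primary objective counts it. The two later visits, which the Hypothesis names, have no check. Nothing therefore supports the claim that the blind *remains* in place, or that the assessors are still blind, at those visits.

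**4. Whose blind is checked?** Outcome measurements gives all measures to a single blinded occupational therapist. The section on the Budapest criteria gives that assessment to an orthopaedist with hand surgery training. The questionnaire names only participants and the evaluator, so it is not clear that the person making the CRPS diagnosis is asked at all.

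**5. How much can one questionnaire show?** Assume a forced two-way guess (the response options are not given) and 30 respondents per arm. With a proportion q guessing correctly, a per-arm blinding index is 2q − 1, and its 95% half-width is 1.96 × 2 × √(q(1 − q)/30).

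- q = 0.50: 1.96 × 2 × √(0.25/30) = 0.36
- q = 0.75: 1.96 × 2 × √(0.1875/30) = 0.31

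This would reveal gross unblinding. It could not establish that the blind held.

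**The case against.** **The control arm is active and the plan does take steps.** Both arms have the same four sessions, written materials and a home programme. The missing sham is disclosed and the blind is tested. Hiding which programme is experimental is feasible under these conditions. This stands: a reader might infer that no masking of participants is possible, but the documents do not show that. Whether masking to the hypothesis succeeds depends on what the consent text says about the other arm, and that text is not shown. What fails is the stronger claim of blinding to allotment.

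**Cast removal is a reasonable time to ask participants.** It is the end of the six-week intervention, when each woman has experienced her whole treatment, and a later guess would be mixed with perceived benefit. This also stands. A reader might infer that the questionnaire is mistimed, or that it never coincides with a primary outcome, but neither is right. Only the narrower point survives: nothing is checked afterwards.

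**Might the questionnaire itself bias later scores?** A reader might suppose that asking about allocation makes women think about their arm before the last two visits. Nothing in the documents shows this, and it forms no part of the point.

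**Might the effect be expressed as a false-positive rate?** With 30 per group, a two-sample t-test at two-sided 0.05 and no true effect, a pure expectation shift of 0.1 to 0.3 SD would give p < 0.05 in about 7% to 21% of trials. That range of shifts is assumed and has no source in the documents. The result describes the consequence of not blinding participants in a therapy trial. It does not measure the wording error, and the change proposed here would not reduce it.

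**Conclusion.** The claim that participants are blinded to allotment contradicts the protocol's own description of the arms and should be withdrawn. At best, participants do not know which programme is under investigation. PRWHE and SF-MPQ are exposed to expectation; the Budapest diagnosis is partly exposed and partly protected by the requirement for observed signs. The size of any bias cannot be derived from the documents.

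The timing point is secondary. Two of the three primary-outcome visits from cast removal onwards have no check on the blind, and they are the two named in the Hypothesis. This does not make cast removal the wrong time for the participant guess, and it does not show that the assessors' blind fails.

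The conclusion rests on the treatment descriptions alone and on no assumed effect size. It is worth correcting because it changes how the self-reported primary results should be read, and the correction is cheap.

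**What to change.** 1. In Participants, replace the blinding claim with wording such as: *participants are not told which programme is under investigation; outcome assessors are blinded*. Describe the trial as assessor-blind throughout.
2. In Limitations, link the missing sham to its consequence: conclusions from the self-reported primary outcomes are limited because women know which programme they perform.
3. Keep the participant guess at cast removal.
4. Add an allocation guess, with the reason for it, at the end of the existing 12-week visit after all measures are complete. It should be given by the evaluator and by the orthopaedist who makes the Budapest assessment.
5. Report all guesses by arm beside the primary results.

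The cost is a few sentences of protocol text and one extra short form for two assessors, with no added visit. The change does not remove expectation effects. It makes the claim accurate and shows whether the assessors' blind lasted to the final visit.
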